### Secondary outcome measures

Quality of life will be assessed using the Short Form-36 (SF-36) Questionnaire [23]. Neck pain will be assessed using the McGill Pain Questionnaire [24]. The recovery period is defined as the number of days from the beginning of treatment to recovery of cervical physiological function and will be recorded by the outcome assessors. Relapse of neck pain will be recorded by telephone investigation during the follow-up period.

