**Methods/Design:**

We will conduct a randomized, double-blind, parallel-group, placebo-controlled trial comparing active acupuncture with placebo (sham acupuncture). A total of 456 patients with neck pain caused by cervical spondylosis who meet the eligibility criteria from outpatient clinics of the Second People’s Hospital of Fujian Province and the Affiliated Rehabilitation Hospital, Fujian University of Traditional Chinese Medicine will be recruited and randomized into an active acupuncture or sham acupuncture group. The participants will undergo treatment sessions with either active or sham acupuncture intervention five times a week for 2 weeks. Evaluation by blinded assessors at baseline and at intervention for 1 and 2 weeks will include demographic characteristics, validated questionnaires (Northwick Park Neck Pain Questionnaire (NPQ) scale, Short-Form 36 (SF-36) scale, and McGill pain scale), examination of neck physiological function, and adverse events. All included patients will be followed up and investigated for relapse of neck pain at 4, 8, and 12 weeks after intervention.

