### Intervention regimen

Patients will be required undergo ten treatment sessions at a frequency of five sessions a week, and the intervention will be completed in 2 weeks. All electroacupuncture procedures will be performed with a Hwato brand SDZ-II electronic needle therapy instrument made by Suzhou Medical Products Factory Co., Ltd. The two groups will be separated from the treatment, which will be performed by a single acupuncturist.

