### Outcome measurement

The following baseline descriptive data will be obtained by questionnaire and physical examination: age, sex, marital status, education level, employment status, family history of CS, VAS score of cervical pain, function of cervical vertebrae, and previous health problems. The radiographic severity of cervical vertebral changes will be assessed on X-ray images. A summary of all measures in the trial is shown in Table 1.

**Table 1 T1:** Study assessments, procedures, and timetable

**Items**	**Before grouping**	**First intervention period (5 days/week)**		**Second intervention period (5 days/week)**		**Follow-up Period**		
Time point (day)	0	1 to 7	7	8 to 14	14	42	70	98
Case diagnosis	X							
Inclusion criteria	X							
Exclusion criteria	X							
Informed consent	X							
Baseline information log	X							
Physical examination	X							
Visual analog scale score	X							
Randomization allocation	X							
Neck physiological function examination		X		X				
Intervention and record		X		X				
Adverse events record		X		X				
McGill pain score			X		X			
Northwick Park Neck Pain Questionnaire score	X		X		X			
Short-Form 36 measure	X		X		X			
Neck pain relapse					X	X	X	X

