### Statistical analysis

The primary outcomes will undergo intent-to-treat analysis based on the initial treatment assignment and focus on assessment of the main effects of the acupuncture treatment for CS at symptoms of CS and function of the cervical vertebrae. Analyses will be performed using IBM SPSS 20 (version 20.0, IBM Corp., New York, NY, USA). The continuous variables and descriptive values will be expressed using means with standard deviations or medians with ranges. For the variables with a normal distribution, statistical comparisons between the groups will be made by using a *t* test. If the variables have a non-normal distribution or ordinal level, statistical comparison between groups will be made using the Mann–Whitney *U* test. Measures with a discrete distribution will be expressed as percentages and analyzed by the *χ*^2^ or Fisher’s exact test as appropriate. The amount of extra diclofenac sodium used between the experiment and control groups will be analyzed, and a general linear model will be applied to adjust its confounding influence if necessary.

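### The recovery period is a time to event seen only to about day 14, but the listed t and Mann-Whitney tests have no place for patients who have not recovered by then

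*Protocol article*

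**What the plan says.** All references are to the protocol article.

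- **Secondary outcome measures** defines the variable: "The recovery period is defined as the number of days from the beginning of treatment to recovery of cervical physiological function". It assigns no value to a patient in whom that recovery is not seen.
- **Outcome measurement, Table 1** has a row "Neck physiological function examination", marked in the columns for days 1 to 7 and 8 to 14 and nowhere else. The follow-up columns (days 42, 70 and 98) carry only the relapse question.
- **Intervention regimen** confirms the length of that window: "the intervention will be completed in 2 weeks".
- **Statistical analysis** assigns tests by type of variable. For continuous measures: "For the variables with a normal distribution, statistical comparisons between the groups will be made by using a" t test, with the Mann-Whitney U test for non-normal or ordinal measures. Percentages go to a chi-square or Fisher's exact test, and a general linear model is held in reserve to adjust for diclofenac use. No time-to-event method is named. Intention-to-treat is attached to the primary outcomes only.

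**The concern.** A count of days to recovery exists only once recovery has happened. Observation of function ends at about day 14, so the variable is right-censored there. A t or Mann-Whitney test on the recorded counts leaves out every patient still impaired at the end of treatment.

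Whether a patient is left out depends on the treatment. If acupuncture works, it brings more patients to recovery, so the two groups of recoverers are no longer comparable as randomised. Two losses follow. The main one is that the difference in how many patients recover, which is likely to be much of the effect, does not enter the test. The second is that the extra recoverers in the better arm may be slow ones, who lengthen that arm's mean and can mask or reverse the comparison. At stake is whether this secondary outcome can show a benefit that is there.

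**Working it through.** **Plan's own figure.** The article states no recovery rate, expected recovery time or power for this outcome, so there is nothing to reproduce. Its 198 per group and 456 in total belong to the NPQ comparison. From them I take only a group size after the stated 15% dropout: 456 × 0.85 / 2 = 193.8, or 194 per arm.

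**Scenario A (assumed): constant daily recovery hazards, 0.08 active and 0.055 sham, observation to day 14.**

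Recovered by day 14, 1 − exp(−14λ):
- active: 1 − exp(−1.12) = 0.674, about 131 of 194
- sham: 1 − exp(−0.77) = 0.537, about 104 of 194

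Mean days among recoverers, 1/λ − 14·exp(−14λ) / [1 − exp(−14λ)]:
- active: 12.50 − 14 × 0.326/0.674 = 5.7 days
- sham: 18.18 − 14 × 0.463/0.537 = 6.1 days

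The hazards differ by a factor of 0.08/0.055 = 1.45, but the means among recoverers differ by only 0.4 day. Most of the effect lies in the 13.7 percentage points (67.4 − 53.7) that this comparison discards.

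Simulated power, two-sided 5%, 2,000 or more trials per run:

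| Analysis | Patients used | Power |
|---|---|---|
| t test on days | recoverers only | about 12% |
| Mann-Whitney on days | recoverers only | 11% to 12% |
| t test, unrecovered set to 14 days | all | about 76% |
| Mann-Whitney, unrecovered ranked worst | all | about 79% |

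Repeated runs of the last row gave 79% to 81%, which is simulation error. The third row shows that the loss comes from dropping the unrecovered, not from the choice between the two tests. Among recoverers, the t test significantly favoured sham in about 0.3% of runs, so there is no reversal in this scenario.

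**Scenario B (assumed): what reversal would need.** Suppose 30% recover under either treatment, with a mean of 5 days on active and 6 on sham. A further share f recovers only under active, with a mean of 11 days. Active is then never worse for any group. The mean among active recoverers is (0.30 × 5 + f × 11) / (0.30 + f); sham stays at 6.0.

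| f | Active mean | Sham mean | t test significantly favours sham | Worst-rank Mann-Whitney favours active |
|---|---|---|---|---|
| 0 | 5.0 | 6.0 | not run | not run |
| 0.05 | 5.9 | 6.0 | 1% | 25% |
| 0.10 | 6.5 | 6.0 | 15% | 51% |
| 0.20 | 7.4 | 6.0 | 81% | 90% |

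(198 per arm, 3,000 runs per simulated row; t test on recoverers only.) The means are equal when 1.5 + 11f = 1.8 + 6f, that is f = 0.06. By f = 0.10 the wrong direction is visible, and at f = 0.20 it dominates. The worst-rank analysis never significantly favoured sham.

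**The case against.** The strongest reply is that the article never says it will drop unrecovered patients. The Statistical analysis section sorts tests by variable type and does not name the recovery period. One of the tests it lists, Mann-Whitney, is also one of the remedies below. What is absent is a rule for scoring the unrecovered, and a full protocol or analysis plan not shown here could supply it. The first part stands: the restriction to recoverers follows from the definition and the listed tests and is not an announced decision. It does not remove the point. The article itself fixes a variable with no value for these patients, lists methods that need a value, and attaches intention-to-treat to other outcomes. A later document would have to add to that text to repair it.

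It is also fair that every rate used here is assumed, and that reversal needs an active arm with many slow extra recoverers. Reversal is a possibility, not a prediction.

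A reader might extend the argument to relapse, inferring that relapse exists only for recovered patients and that the planned chi-square test would therefore favour the worse arm. The documents do not support this. The abstract says "All included patients will be followed up and investigated for relapse of neck pain at 4, 8, and 12 weeks after intervention". Recovery is defined on neck function and relapse on neck pain, and nothing makes the first a condition of the second. An endpoint combining the two would be a new outcome, not a correction. The relapse mark at day 14 in Table 1 is a clerical matter and has no bearing on this point.

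**Conclusion.** The point holds for the recovery period alone. As defined and with the methods listed, the comparison falls on patients who recovered within about 14 days, a subset formed after randomisation by the outcome itself. Under assumed hazards of 0.08 v 0.055 per day and 194 per arm, that costs most of the power: about 12% instead of about 79%. A reader might infer that the analysis will point the wrong way. That is too strong: it does not happen under those hazards, and it appears only under other assumptions in which roughly 10% or more additional active-arm patients recover late. The likelier harm is a missed effect. This is one secondary outcome; the NPQ analysis and the sample size are untouched. The change should be made, but the trial does not depend on it.

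**What to change.** State that the recovery period is analysed in all randomised patients, by one of two methods named in advance:

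1. Time to event: patients not recovered are censored at their last function examination, with Kaplan-Meier curves and a log-rank test, or a discrete-time model if recovery is known only at scheduled examinations.
2. Mann-Whitney U test with unrecovered patients ranked worst, which keeps a test that the article already lists.

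Report the proportion recovered in each arm alongside either. The cost is a few lines of analysis wording. No extra visits, data or patients are needed, and neither the relapse outcome nor the primary analysis changes.

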### Safety evaluation

Any adverse events (defined as any functional lesion caused by the interventions, such as local bleeding at the needle insertion point; local numbness, pain, or dizziness during treatment and so on) will be recorded during treatment. If any adverse event occurs, the doctor will provide the corresponding treatment to the patient. The adverse events will be immediately reported to the primary investigator and ethics committee to decide if the patient needs to withdraw from the trial.

### Data collection and management

The demographic and baseline characteristic data will be collected by screeners when the patients are recruited. Clinical outcome measurement and questionnaire-based assessment of treatment effects and neck physiological function will be measured by the outcome assessors after the treatment is completed. During the follow-up period, relapse of neck pain will be investigated by a telephone call at 4, 8, and 12 weeks post treatment.

Research assistants will conduct quality control of data collection and be responsible for data entry. The data manager will be responsible for initial data cleaning, identifying, coding, and conversion into the proper format for data analysis.

### Statistical analysis

The primary outcomes will undergo intent-to-treat analysis based on the initial treatment assignment and focus on assessment of the main effects of the acupuncture treatment for CS at symptoms of CS and function of the cervical vertebrae. Analyses will be performed using IBM SPSS 20 (version 20.0, IBM Corp., New York, NY, USA). The continuous variables and descriptive values will be expressed using means with standard deviations or medians with ranges. For the variables with a normal distribution, statistical comparisons between the groups will be made by using a *t* test. If the variables have a non-normal distribution or ordinal level, statistical comparison between groups will be made using the Mann–Whitney *U* test. Measures with a discrete distribution will be expressed as percentages and analyzed by the *χ*^2^ or Fisher’s exact test as appropriate. The amount of extra diclofenac sodium used between the experiment and control groups will be analyzed, and a general linear model will be applied to adjust its confounding influence if necessary.

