**Discussion:**

This paper describes the rationale and design of a randomized double-blind, placebo-controlled trial that aims to determine the efficacy and safety of acupuncture intervention for neck pain caused by cervical spondylosis. The primary outcomes are changes in the NPQ score and neck physiological function. Secondary outcome measures include quality of life, adverse events, and relapse of neck pain. If successful, this project will provide evidence of the efficacy and safety of acupuncture for neck pain caused by cervical spondylosis.

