### Sample size

The sample size calculation was based on a reference of a similar intervention in similar patient groups using the same primary outcome instrument [21]. The primary outcome measure is improvement of scores in neck pain as measured with the Northwick Park Neck Pain Questionnaire (NPQ) at the end of treatments. According to previous research [21], the mean and standard deviation of NPQ scores were (24.04 ± 11.83) in the placebo group and (20.71 ± 11.91) in the acupuncture group. The sample size was calculated based on the formula:

(1)$$n_{1}=n_{2}=2{\left(\frac{z_{\alpha /2}+z_{\beta }}{M_{e}-M_{c}}\right)}^{2}\delta^{2}$$

with a type I error of 5% (α = 0.05) and 80% power (β = 0.2). A total of 198 patients are required in each group to show statistical differences between the groups. We estimated that 15% patients will drop out of the study; thus, 456 patients was established as the sample size.

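### The primary NPQ comparison is valid but uses no baseline covariate and lets the observed distribution choose the test; one prespecified ANCOVA on day-0 NPQ would be more precise at almost no cost

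*Protocol article*

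**What the plan says.** The Statistical analysis section gives one rule for all continuous variables, the primary outcome included. The branch that leads to the *t* test reads "For the variables with a normal distribution, statistical comparisons between the groups will be made by using a". The other branch, which leads to the Mann–Whitney *U* test, reads "If the variables have a non-normal distribution or ordinal level, statistical comparison between groups will be made using the". No baseline covariate is named in either. The only model mentioned is a general linear model for diclofenac use, to be fitted if needed; that is a post-randomisation variable, not a baseline one.

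Table 1 schedules the NPQ at day 0, day 7 and day 14. SF-36 has the same three time points.

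The primary outcome is worded as change. The Abstract says "The primary outcomes are changes in the NPQ score and neck physiological function". Primary outcome measures also speaks of changes, and Sample size speaks of improvement in NPQ at the end of treatment. The figures used for sizing, however, are score levels: "the mean and standard deviation of NPQ scores were (24.04 ± 11.83) in the placebo group and (20.71 ± 11.91) in the acupuncture group". They cannot be improvements, because the placebo mean is the larger one and the figures would then favour placebo.

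**The concern.** Three features of the plan bear on the same comparison.

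- **Baseline is collected but not used as a covariate.** A two-sample test on final scores makes no use of day-0 NPQ. A test on change uses it only by subtraction, with its coefficient fixed at 1. ANCOVA estimates that coefficient, is at least as precise as either in a trial of this size, and corrects for chance baseline imbalance.
- **The observed distribution selects the test.** A *t* test compares means and Mann–Whitney compares ranks. Under the stated rule, the effect measure for the primary outcome is not settled until the data have been inspected.
- **The quantity named and the quantity sized differ.** The outcome is change, while the SDs are those of scores. If change is what is tested, the stated power does not carry over automatically.

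At stake is precision in a trial planned for 80% power with no visible margin, and a primary result whose scale is not fixed in advance.

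**Working it through.** **Inputs from the protocol.** Means 24.04 and 20.71, so the difference is 3.33. SDs 11.83 and 11.91, so the pooled SD is √[(11.83² + 11.91²)/2] = 11.87. Two-sided α 0.05, power 80%, 198 per arm, 15% dropout, 456 in total.

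**Assumptions not in the protocol.** The correlation r between baseline and final NPQ, shown for 0.3 to 0.7, and equal SDs at baseline and day 14 (relaxed below).

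**Step 1: reproduce the stated figure.** n per arm = 2 × [(1.960 + 0.842)/3.33]² × SD².
- SD 11.83 gives 198.1
- SD 11.87 gives 199.5
- SD 11.91 gives 200.8

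The stated 198 therefore comes from score-level SDs. Power at 198 per arm with SD 11.87 is 79.7% by the normal approximation.

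**Step 2: number expected to complete.** 456 × 0.85 / 2 = 193.8, or about 194 per arm.

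**Step 3: effective SD of each analysis.**
- Final score: 11.87
- Change score: 11.87 × √[2(1 − r)]
- ANCOVA on baseline: 11.87 × √(1 − r²)

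**Step 4: power at 194 per arm.** Two-sided, noncentral *t*, noncentrality = 3.33 / (effective SD × √(2/194)).

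| r (assumed) | SD of change | ANCOVA SD | Change *t* test | Final-score *t* test | ANCOVA |
|---|---|---|---|---|---|
| 0.3 | 14.04 | 11.32 | 64.4% | 78.7% | 82.4% |
| 0.4 | 13.00 | 10.88 | 71.1% | 78.7% | 85.2% |
| 0.5 | 11.87 | 10.28 | 78.7% | 78.7% | 88.9% |
| 0.7 | 9.19 | 8.48 | 94.5% | 78.7% | 97.1% |

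By the normal approximation, the number per arm for 80% power at r = 0.3, 0.5 and 0.7 is 280, 200 and 120 for change, 200 throughout for final scores, and 182, 150 and 102 for ANCOVA.

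**Step 5: relax the equal-SD assumption.** Let the baseline SD be k times the final SD. The variance of change is SD²(1 + k² − 2rk), which equals SD² when r = k/2. The break-even correlation is therefore 0.4 if k = 0.8, 0.5 if k = 1 and 0.6 if k = 1.2. At 198 per arm (normal approximation), change-score power at r = 0.3, 0.5 and 0.7 is:
- k = 0.8: 73.6%, 86.1%, 97.2%
- k = 1: 65.5%, 79.7%, 95.0%
- k = 1.2: 56.7%, 70.8%, 89.3%

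The ANCOVA SD does not depend on k. The change-score variance exceeds the ANCOVA variance by SD²(k − r)², which is never negative, so the ranking does not rest on equal SDs.

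**The case against.** The case on the other side has real force.

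- **No bias is shown.** An unadjusted intention-to-treat comparison of randomised groups is unbiased and controls type I error. ANCOVA is a gain in efficiency. This stands.
- **Covariates are often left to the analysis plan.** This would excuse silence, but the article is not silent: it names the tests and the rule for choosing between them.
- **The mismatch depends on the reading.** The Statistical analysis section does not say whether final or change scores are tested. If final scores are compared, the sizing SDs fit the test and power is about 79% whatever the correlation. This stands.
- **The test-choice rule costs little power.** No formal normality pre-test is named, and a comparison of means is robust at about 200 per arm. If the data are normal, Mann–Whitney has about 95.5% efficiency, so 198 per arm gives 77.9% against 79.7%. The unsettled effect measure remains, as a minor point.

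A reader might infer that the trial is underpowered for its primary outcome. The documents do not support that: the correlation and the baseline SD are not given, and a change score gains power once r exceeds the break-even value. A reader might also infer that baseline NPQ is ignored altogether. That is exact only for a final-score comparison; a change score uses it by subtraction.

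**Conclusion.** The point holds as a recommended improvement. The planned tests are valid but less precise than ANCOVA, and the rule for choosing between them leaves the primary effect measure open. Over an assumed correlation of 0.3 to 0.7 at 194 per arm, ANCOVA gives 82.4% to 97.1% power, against 78.7% for final scores and 64.4% to 94.5% for change. It is the only one of the three above 80% across that range. Its advantage over final scores vanishes as r approaches 0, and its advantage over change shrinks as r rises.

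That ANCOVA is at least as precise does not depend on the assumed values, apart from one degree of freedom, which is negligible here. The size of the gain does depend on them. Any statement that a change-score analysis falls short of 80% power is conditional on r and on the ratio of the SDs, and can go either way.

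**What to change.** Prespecify, before unblinding, a single primary NPQ analysis: a linear model of day-14 NPQ on randomised group and baseline NPQ, reporting the adjusted mean difference with its 95% CI. Use it whatever the distribution looks like, and keep the Mann–Whitney *U* test as a sensitivity analysis. With baseline in the model, the adjusted group difference is the same whether day-14 score or change is the response, so the wording of the outcome as change can stay.

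Use the same approach for SF-36, which also has a day-0 value. Adding hospital as a covariate is optional.

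The cost is a sentence or two in the analysis section. Baseline NPQ is already collected, the SPSS version named in the protocol can fit the model, and neither the sample size nor the visit schedule has to change on this account.

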### Inclusion criteria

To be eligible, participants must fulfill the following criteria: (1) a confirmed diagnosis of CS neck pain in accordance with the diagnostic criteria published by the Chinese Association of Rehabilitation Medicine (2010) [20] and with reference to the *International Classification of Diseases,* 10th edition (ICD-10) codes (http://www.icd10data.com): M47.812 (other spondylosis without myelopathy or radiculopathy (cervical region)); (2) male or female 18 to 60 years of age; (3) with/without positive signs of musculoskeletal system upon physical examination; (4) pain intensity ranging from 3 to 7 points on a visual analog scale (VAS) upon recruitment; (5) no acupuncture or other relative treatment within the last 7 days; and (6) informed consent document has been signed.

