### Interventions

The intervention scheme originates from the guidelines of diagnosis, treatment, and rehabilitation for CS [20] and has been practiced for some time in the Second People’s Hospital of Fujian Province and the Affiliated Rehabilitation Hospital, Fujian University of Chinese Medicine. We hypothesized that acupuncture for CS neck pain would have a more positive effect in terms of relieving neck pain and recovering neck physiological function than placebo (sham acupuncture). Therefore, participants in the experimental group will receive the active acupuncture treatment, and participants in the control group will receive the sham acupuncture treatment. All participants will receive 25 mg of diclofenac sodium three times a day if their VAS scores exceed 5.

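### Adjusting the treatment comparison for diclofenac use, as if it were a confounder, can remove part of the acupuncture effect

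*Protocol article*

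**What the plan says.** The Interventions section of the protocol article sets the drug rule: "All participants will receive 25 mg of diclofenac sodium three times a day if their VAS scores exceed 5". It gives no time window for the trigger. The same section states the hypothesis that acupuncture "would have a more positive effect in terms of relieving neck pain and recovering neck physiological function than placebo".

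The Statistical analysis section first commits to the randomised comparison: "The primary outcomes will undergo intent-to-treat analysis based on the initial treatment assignment". It names a t test, or a Mann-Whitney U test for non-normal or ordinal variables. It closes with diclofenac: "The amount of extra diclofenac sodium used between the experiment and control groups will be analyzed", after which "a general linear model will be applied to adjust its confounding influence if necessary". It does not define when adjustment is necessary, and it does not say whether the adjusted or the unadjusted result prevails.

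Two other places bear on when the trigger operates. Inclusion criterion 4 requires "pain intensity ranging from 3 to 7 points on a visual analog scale (VAS) upon recruitment", and Table 1 (Outcome measurement) schedules VAS at day 0 only.

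**The concern.** Allocation is randomised, so drug use that builds up afterwards cannot confound the comparison of arms. If use follows pain during treatment, it lies downstream of treatment. On the trial's own hypothesis, fewer active patients would exceed VAS 5 and they would take less diclofenac. The difference in use is then partly the treatment effect, and conditioning on it takes that part away.

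The undefined trigger makes this worse. The natural prompt for adjusting is a difference in use between arms, which the plan examines immediately beforehand. That difference is likeliest when acupuncture works, so the model would tend to be invoked when it does most damage. With planned power of only 80%, there is little room to lose.

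**Working it through.** **Inputs from the Sample size section.** NPQ 24.04 (SD 11.83) for placebo and 20.71 (SD 11.91) for acupuncture; two-sided α = 0.05; power 80%; 198 per group. Difference = 24.04 − 20.71 = 3.33. Mean SD = (11.83 + 11.91)/2 = 11.87.

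**Reproducing the plan's figure.** n = 2 × (1.960 + 0.842)² × (11.87/3.33)² = 199.5, so 200 per group (199 with SD 11.83, 201 with SD 11.91). This agrees with 198 to within 3%. Power at 198 per group is 79.7%. The figure is not in dispute; it is the reference point.

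**Assumed model (every diclofenac input is an assumption).**
- Standardised pain during treatment is normal with SD 1. The active arm is shifted down by δ = 3.33/11.87 = 0.28.
- A patient uses diclofenac if pain exceeds a cut-off t, chosen so that a share p0 of sham patients use it. The active share is p1 = 1 − Φ(t + δ).
- Pain and NPQ have within-arm correlation ρ. Diclofenac itself has no effect on NPQ (relaxed below).

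The within-arm slope of NPQ on use is

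b = 11.87 × ρ × [φ(t) + φ(t + δ)] / [p0(1 − p0) + p1(1 − p1)]

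and the adjusted difference is 3.33 − b × (p0 − p1).

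**One case in full (ρ = 0.3, 20% sham use).** t = 0.842 and t + δ = 1.122, so p1 = 13.1%. The densities sum to 0.280 + 0.213 = 0.493. The denominator is 0.160 + 0.114 = 0.274. So b = 11.87 × 0.3 × 0.493/0.274 = 6.4, and the adjusted difference is 3.33 − 6.4 × 0.069 = 2.89, which is 13% smaller.

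**All cases: adjusted NPQ difference (shrinkage).**

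| Use, sham vs active | ρ = 0.1 | ρ = 0.3 | ρ = 0.7 | Chance that use differs by arm at p < 0.05 |
|---|---|---|---|---|
| 5.0% vs 2.7% | 3.27 (2%) | 3.15 (5%) | 2.90 (13%) | 22% |
| 10.0% vs 5.9% | 3.23 (3%) | 3.04 (9%) | 2.65 (21%) | 32% |
| 20.0% vs 13.1% | 3.18 (4%) | 2.89 (13%) | 2.30 (31%) | 46% |
| 50.0% vs 39.0% | 3.12 (6%) | 2.70 (19%) | 1.86 (44%) | 60% |

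The last column is the power of a two-proportion test at 198 per group. Simulating 8,000 trials at 5%, 20% and 50% sham use gave 21%, 46% and 59%. If use were fixed at entry, the figure would be about 5%.

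**Power after adjustment.** The calculation credits the model with the smaller residual SD. In the worst cell (ρ = 0.7, 50% use), b = 13.3, so the residual variance is 11.87² − 13.3² × 0.244 ≈ 97.6 and the residual SD is 9.9. The standard error is about 1.00, and power is Φ(1.86/1.00 − 1.96) ≈ 46%. In the mildest cell (ρ = 0.1, 5% use) it is 78%.

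**Allowing diclofenac to lower NPQ.** If it lowers NPQ by g points among users, the unadjusted difference becomes 3.33 − g(p0 − p1), while the adjusted difference stays as tabulated. The adjusted figure is closer to 3.33 once g exceeds b. That break-even is 2.7, 2.4, 2.1 and 1.9 points down the table for ρ = 0.1, and 8.0, 7.2, 6.4 and 5.7 points for ρ = 0.3. With ρ = 0.1, 20% use and g = 3, the unadjusted difference is 3.33 − 3 × 0.069 = 3.12, against 3.18 adjusted.

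**Amount instead of yes/no.** The plan speaks of amount. Taking days of use out of 10 treatment days, an assumed day-to-day pain correlation of 0.7, ρ = 0.3 and 1,000,000 simulated patients, shrinkage is about 14%, 27% and 35% at 5%, 20% and 50% of sham days. The yes/no model gives 5%, 13% and 19%.

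**A second simulation.** This one assumed entry VAS uniform from 3 to 7, use on weeks with VAS above 5, and a total NPQ effect of about 3.2 before any drug effect. The ratio of adjusted to total effect was:

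| Drug effect, NPQ points per day of use | 0 | 0.2 | 0.5 | 1.0 | 1.5 |
|---|---|---|---|---|---|
| Use follows VAS in weeks 1 and 2 | 0.53 | 0.57 | 0.65 | 0.82 | 1.11 |
| Use follows week-1 VAS only | 0.76 | 0.80 | 0.88 | 1.05 | 1.30 |
| Use fixed by entry VAS | 1.00 | 1.00 | 1.00 | 1.00 | 1.00 |

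Neck function, the other primary outcome, cannot be computed because the article gives no figures for it.

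**The case against.** The premise is not settled. Table 1 schedules no VAS after day 0, and the entry range of 3 to 7 straddles the cut-off of 5, so the drug rule can be read as an entry rule. On that reading adjustment does no harm. This stands as a condition on the finding. Against it, an extra amount that is used and then compared between arms reads more naturally as use accrued during treatment. Use fixed at entry would differ between arms only by chance and would give little reason to adjust.

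The adjusted model is optional and comes last, after the intent-to-treat commitment and the unadjusted tests, and nothing makes it primary. That also stands, and it limits the severity. However, calling use a confounder is an error in what the text states, not a detail left to an analysis plan, and nothing confines the adjusted result to a supporting role.

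A covariate does not stop patients being analysed in their assigned arm, so this is not a breach of intent-to-treat in the narrow sense. That is fair. The point is that the adjusted contrast no longer estimates the effect of assignment alone.

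Finally, the sizes rest on assumed inputs, the headline range sets the drug effect to zero, and a strong drug effect reverses the direction. All true. Wanting an estimate that accounts for the drug is also legitimate, but a plain covariate for pain-driven use does not in general isolate acupuncture without the drug.

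**Conclusion.** The concern holds, conditionally. If diclofenac use responds to pain during treatment, the plan mislabels a consequence of treatment as a confounder and allows the comparison to be adjusted for it. The expected result is an NPQ difference that is too small. Under the yes/no model with no drug effect, it is 2% to 44% smaller than 3.33, and power is 78% to 46%. These are illustrations over assumed ranges, not measurements from this trial. At the mild end the loss is negligible, and a large enough drug effect reverses it. If use is fixed by entry VAS, there is no distortion and no need to adjust. Because the unadjusted test is the default, this is a point to consider, held with medium confidence.

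**What to change.** Replace the last sentence of the Statistical analysis section with one saying three things: diclofenac use is reported by arm as an outcome; the primary NPQ and neck-function comparisons are not adjusted for it; and any model that includes it is exploratory.

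This costs one sentence and no new data, and it loses nothing if use turns out to be fixed at entry. The trade-off is that the unadjusted comparison estimates acupuncture with diclofenac as needed, not acupuncture alone. That matches the drug rule the Interventions section applies to both arms.
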